### Inclusion and Exclusion Criteria

#### Phase 1

The inclusion criteria are (1) age 6-59 months, (2) both sexes, (3) resident of the study area, (4) WHZ≤–3 SD without any signs of complications (uncomplicated SAM), and (5) passing the appetite test.

Children with SAM who have medical complications or infection have loss of appetite due to underlying physiological changes. The appetite test helps identify such children. Every child identified as having SAM during growth monitoring will undergo the appetite test to decide the further course of treatment. In Telangana, Balamrutham Plus is used under the SSFP for the test. The quantity provided varies by age: age 7-18 months, at least 15 g; age 19-36 months, 30 g; and age 37-59 months, 50 g. Children who are able to consume the given quantity are considered to have passed the test and are enrolled in the SSFP; otherwise, they are referred to a nutrition rehabilitation center for further treatment. The test usually takes a short time but may even take up to 1 hour [20].

The exclusion criteria are (1) WHZ≥–2 SD, between –2 SD and –3 SD, or <–3 SD with complications (children with complicated SAM); (2) bilateral pitting edema; (3) congenital anomalies, inborn errors of metabolism, or developmental delay; and (4) malabsorption syndromes.

Children with SAM will be identified from the NHTS through the district health administration. During the study period, all eligible children will be contacted to participate in the study.

#### Phase 2

Primary caregivers of children aged 6-59 months with uncomplicated SAM will be identified based on their volunteerism and participation. Each FGD will include 8-10 participants, and 10-12 FGDs will be conducted, in addition to 2 IDIs in each health care worker group: ASHA, *Anganwadi* teacher (center), ANM (subcenter), MO (PHC), and pediatrician (district hospital and tertiary care center). The number of FGDs and IDIs will be based on the level of information saturation.

#### Phase 3

The inclusion criteria are (1) age 6-59 months, (2) enrollment in the SSFP/CMAM program, (3) WHZ <–3 SD or MUAC=115 mm, (4) passing the appetite test using Balamrutham Plus, (5) both sexes, (6) available for the entire 6 months of the study period, (7) no edema, (8) no antibiotic use in the past 1 month, (9) no clinical complications requiring antibiotic treatment and/or inpatient care, and (10) primary resident of the catchment area. Children who participate in phase 1 will also be eligible to be part of phase 3.

The exclusion criteria are (1) complicated cases of SAM and (2) antibiotic use in the past 1 month.

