### Rationale of the Study

In 2023, the Government of India released the National Protocol for Management of Malnutrition in Children to strengthen the ongoing efforts and commitment to address the challenges of malnutrition [18]. Mission Saksham Anganwadi and Poshan 2.0 was launched to drive the efforts to reduce malnutrition by identifying and managing children aged <5 years with SAM in India [19]. Under this program, peripheral health workers and *Anganwadi* (rural child care center in India) teachers are trained to make initial decisions on the level of inpatient or community-based care, nutrition management, and follow-up care for the identified children aged <5 years with SAM. These children are enrolled for CSAM at *Anganwadi*s and administered empirical amoxicillin for 5 days, twice a day, along with nutritional support for 4 months [20].

Although empirical antibiotics are currently in use, recent studies from the Africa region and one from India have not found them effective in improving nutritional recovery [21]. The potential reason was either a low rate of infection among children with uncomplicated SAM at the time of identification or AMR emergence, making empirical antibiotics ineffective [22-24]. Thus, the context-specific relevance of empirical antibiotics needed to be tested by assessing infection rates among children with uncomplicated SAM at the time of identification and by exploring antibiograms.

In India, a few observational studies in tertiary care hospitals among children with complicated SAM have reported a high prevalence of diarrhea (36%), fever (34%), and pneumonia (43%) [25-27]. However, this evidence does not warrant the use of empirical antibiotics among children with uncomplicated SAM managed at the community level without any clinical symptoms of infection. In addition, there is a lack of evidence on the burden of clinical/subclinical infection among children with uncomplicated SAM in India, and it is important to decide whether empirical antibiotics are necessary for this patient group.

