### Study Area

Phase 1 of the study will be conducted in Yadadri Bhuvangiri District, Telangana, India [38]. The district has a population of ~800,000, with 16% urban, 80% rural, and some tribal populations, with ~300 villages and 1 municipal corporation area. According to the 2011 Census, this district had 50,000 tribal people. Every month, ~50 new children with uncomplicated SAM and ~100 children with moderate acute malnutrition (MAM) are identified by *Anganwadi* teachers during routine monthly growth-monitoring drives, and the data are entered on the website of the Nutrition and Health Tracking System (NHTS) of the state government under the Supervised Supplementary Feeding Programme (SSFP) [20]. The identified children are provided with locally available nutrient- and energy-dense food, Balamruthuam Plus, an enhanced ready-to-use therapeutic food. Children with MAM receive this food for 2 months, while children with uncomplicated SAM receives it for 4 months. All children with uncomplicated SAM are administered a weight-adjusted dose of amoxicillin twice daily for 5 days.

Phase 2 of the study will be conducted both in the community and the hospital. In the community, caregivers of children with uncomplicated SAM will be contacted for participation in the FGDs. Caregivers who participate in the quantitative study on clinical/subclinical infections and AMR will be eligible for this phase. In the hospital setting—which includes primary health centers (PHCs), subcenters, and district and tertiary care centers—various health care providers, such as medical officers (MOs), auxiliary nurse midwives (ANMs), and pediatricians, will be contacted to participate in the study. IDIs will be conducted with them.

Phase 3 of the study will be carried out in the community via house-to-house visits, initially in Yadadri Bhuvangiri District and later in further districts as the sample gets saturated.

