#### Follow-Up Visits

Children will be followed up monthly during the intervention, in addition to follow-up postdischarge from the program at 4 and 6 months. Telephone calls will be made once every 15 days to document any illness, medication use, or side effects. Physical visits will be made every 30, 60, 90, 120 and 180 days.

For compliance assessment, empty amoxicillin strips will be collected at 30 days. For azithromycin, single-dose compliance assessment will be performed on the day of enrollment to the RCT. An additional buffer of 5 days will be allowed to collect data at each timepoint. Clinical adverse events of the intervention will be assessed during physical visits and documented over the phone.

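### Phase 3 entry sets no limit on time already spent in the 4-month feeding programme, so part-fed children can enter and the 4-month definitions do not fit them

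*Protocol article*

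**What the plan says.** Under Inclusion and Exclusion Criteria, Phase 3 requires "2) enrollment in the SSFP/CMAM program", "3) WHZ <–3 SD or MUAC=115 mm" and "8) no antibiotic use in the past 1 month", among other items. None of the ten criteria limits time since programme admission. Study Procedure, Phase 3, takes children from a list on the NHTS website and confirms their nutritional category at home. The only window before randomisation is in Table 1: 7 days from collection of baseline data, not from programme admission.

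Study Area describes the programme. The food is given to moderately malnourished children for 2 months, "while children with uncomplicated SAM receives it for 4 months", and every child with uncomplicated SAM also receives a 5-day amoxicillin course.

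On timing, Outcomes counts weight gain from the start of the intervention. Follow-Up Visits describes monthly visits "in addition to follow-up postdischarge from the program at 4 and 6 months". Operational Definitions calls a child a nonresponder if WHZ has not passed -2 SD after 4 months, without saying from when.

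Rationale of the Study says that the relevance of empirical antibiotics should be tested by "assessing infection rates among children with uncomplicated SAM at the time of identification". For Phase 1, the criteria section says "During the study period, all eligible children will be contacted to participate in the study", again with no rule on new admission.

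**The concern.** The schedule reads as if randomisation and programme admission fall together, so that trial month 4 is programme discharge. The entry rule does not secure this. A child in the second or third month of feeding who is still below -3 SD, passes the appetite test and has had no antibiotic in the past month meets the criteria as written.

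Such a child has already shown a slow response to feeding and has less of the ration left. Three things are at stake. The amount of feeding before and during follow-up varies between children. The 4-month status has two possible meanings, programme time or trial time. A null result could come partly from children well past the point at which the programme gives its antibiotic, so it would not clearly answer the policy question about antibiotics at the start of community management.

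**Working it through.** **Inputs from the protocol article**
- Feeding lasts 4 months (Study Area), taken as 120 days.
- Programme amoxicillin lasts 5 days (Study Area). The antibiotic-free period is 1 month (Phase 3 criteria), taken as 30 days.
- The first primary endpoint is at 16 weeks from the start of the intervention (Outcomes): 16 × 7 = trial day 112.
- The last visit is at trial day 180 (Table 1).

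**Assumptions.** The programme course starts at admission, feeding runs from programme admission, and the ration is not restarted at randomisation. The documents settle none of these.

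**Step 1: earliest entry after the programme course.** 5 + 30 = 35 days after admission. A child could enter sooner only if reached before the programme dose, and no section says that dose is withheld.

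**Step 2: feeding left at randomisation.** Let t be days in the programme at randomisation. Feeding left = 120 - t. Days from end of feeding to trial day 112 = 112 - (120 - t) = t - 8. Days from end of feeding to trial day 180 = t + 60.

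| t | Feeding left (days) | At trial day 112 | At trial day 180 |
|---|---|---|---|
| 0 | 120 | 8 days of feeding still to come | 60 days after feeding ended |
| 35 | 85 | 27 days after | 95 days after |
| 60 | 60 | 52 days after | 120 days after |
| 90 | 30 | 82 days after | 150 days after |

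Trial month 4 (day 120) equals programme discharge only at t = 0.

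**Step 3: can the share affected be derived?** About 50 new children a month (Study Area) × 4 months gives up to 200 on the list, of whom 150 are past their first month if none is discharged early. How many are still below -3 SD is not stated. The nearest figures are the 2-week WHZ values in Sample Size, -1.29 (0.84) and -1.45 (0.93). Under normality, (-3 + 1.29)/0.84 = -2.04 and (-3 + 1.45)/0.93 = -1.67, so about 2% and 5% lie below -3. That is 3 to 7 of 150. An assumed 20% to 50% would give 30 to 75 of 150. Beside 50 new children, the range in a first sweep runs from 3/53 = 6% to 75/125 = 60%, which is too wide to be an estimate.

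**Step 4: effect on power (illustration only).** The plan's sample size reproduces: difference 0.16, pooled SD √((0.84² + 0.93²)/2) = 0.886, two-sided 5%, 80% power gives 482 per group against 480 stated. At the planned 250 per group, power is 52%, which is a separate matter. If 10% to 50% of children were part-fed and their mean WHZ differed by 0.25 to 1.0 (assumptions), then SD = √(0.886² + p(1 - p)d²) runs from 0.889 to 1.017, and power at 250 from 52% down to 42%.

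**The case against.** The text hints that entry near admission was intended. The appetite test is the gate to the programme, and Table 1 puts it at trial baseline. Intervention Phase gives the food together with the allocated antibiotic after enrolment. Follow-Up Visits equates 4 months with discharge. The preparatory phase leaves implementation detail to a final protocol and SOPs. This stands as evidence of intent. However, eligibility is listed item by item, and as written it admits part-fed children.

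A reader might infer more than the documents support:
- **That the 16-week endpoint loses its common start.** It does not. It is counted from the start of the intervention, and visits fall on fixed trial days. What differs is feeding before and after that start.
- **That the arms become incomparable.** Within each randomisation stratum, time in the programme is balanced in expectation.
- **That any enrolled child qualifies.** The WHZ or MUAC, appetite, antibiotic and complication criteria all narrow entry.
- **That a large share of the trial is affected.** A backlog matters mainly in the first sweep of a district. Even 75 such children would be 10% of 750, although sweeps may recur as districts are added.
- **That Phase 1 misses its objective.** The objective is prevalence among children with uncomplicated SAM. Assessment at identification appears only in the rationale.

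It is also fair to object that a rule admitting only recent admissions could leave almost no eligible child while the programme course and the 1-month exclusion stand together. That objection is sound and shapes the fix.

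**Conclusion.** The concern holds as a gap in entry and timing. Criterion 2 has no limit on programme time, and the list is not confined to new cases. The 1-month antibiotic exclusion, set against routine programme amoxicillin, can steer recruitment towards children at least about 35 days into feeding.

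For them, feeding ends 27 to 82 days before the 16-week measurement (entry on programme day 35 to 90), the month-4 visit is not at discharge, and 4-month nonresponse has no defined start. The harm is to heterogeneity, to the meaning of the 4-month outcomes and to applicability, not to the fairness of the comparison within strata. Loss of power is probably modest. The day counts rest on a 120-day ration that runs from admission and is not restarted. The number of children affected cannot be derived from the documents.

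**What to change.** 1. Reconcile the 1-month antibiotic exclusion in Phase 3 with the routine programme amoxicillin in Study Area. The choice is the investigators', and it must come first because it decides who can be eligible near admission.
2. Then state in criterion 2 a maximum interval from programme admission to randomisation.
3. Record the NHTS admission date for every child.
4. Count 4-month nonresponse and time to recovery from randomisation, and reword the post-discharge visits to match.
5. If part-fed children are kept, prespecify days since programme admission as a covariate, with a supporting analysis in new admissions.
6. In Phase 1, record the same date and report prevalence by time since admission.

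The cost is a revised criterion, one date field and two clarified definitions. The downside is that part of the existing list may become unusable, so recruitment would lean more on the roughly 50 new children a month and on the further districts that the plan already allows.

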## Introduction

### Background

Acute malnutrition is defined as a condition characterized by a severe nutrient deficit due to inadequate intake of food or the inability of the body to properly absorb essential nutrients [1]. Worldwide, 45.4 million children aged <5 years have wasting [2]. In India, the National Family Health Survey (NFHS)-5 reported a 19.3% burden of wasting and a 7.7% burden of severe wasting [3]. Although the burden of wasting remains almost constant, there is an increase in severe wasting compared to NFHS-4 and NFHS-3 [3-5]. Severe wasting indicates severe acute malnutrition (SAM) and is defined as a weight-for-height z-score (WHZ) of <−3 SD, a mid-upper arm circumference (MUAC) of <115 mm, or bilateral pitting pedal edema [6].

From the management perspective, SAM is further classified into complicated and uncomplicated SAM. Children with complicated SAM exhibit no appetite or have medical complications, while those with uncomplicated SAM have a successful standard appetite test and no fever, clinical infections, or complications [7]. Children with both complicated and uncomplicated SAM have a higher risk for acute infections, such as pneumonia, diarrhea, and sepsis, which triples the mortality risk: a few reported reasons are a weakened immune system, altered gut microbiota, poverty, food insecurity, and inadequate access to health care [8,9]. The fatality rate among children with SAM receiving inpatient care ranges from 3.4% to 35%. These data show that 3.5 million deaths are estimated among children in India aged <5 years [10].

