### Operational Definitions

Children with uncomplicated SAM are clinically well (ie, without signs of infection) and with a retained appetite (passed the appetite test), which is considered indicative of the absence of severe metabolic disturbance. SAM is defined as WHZ<–3 SD of the median WHO child growth standards and/or by the presence of bilateral pitting edema. Nonresponse to treatment is defined as children who do not meet discharge criteria (WHZ>–2 SD) after 4 months.

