### Outcomes

The primary outcomes of the RCT are as follows:

Weight gain at 16 weeks and 6 months after intervention initiationWHZ at 16 weeks and 6 monthsMUAC at 16 weeks and 6 monthsAnthropometric measurements collected by trained study staff using standardized procedures and calibrated equipment: weight measured using digital weighing scales; height/length using stadiometers or infantometers, as appropriate; and MUAC using standardized MUAC tapes

The secondary outcomes include the following:

Time to nutritional recoveryNutritional status at follow-up, categorized as cured (WHZ>−2 SD), nonresponder (WHZ<−2 SD), or lost to follow-upTransfer to inpatient careClinical signs of infection and morbidity episodes, including fever, diarrhea, and respiratory symptomsRecurrent infections during follow-upHemoglobin levelsAdverse events related to antibiotic therapyMortality

Clinical outcomes and morbidity episodes will be assessed during scheduled follow-up visits through caregiver interviews and clinical examination by trained study personnel. Hemoglobin levels will be estimated using standard laboratory methods. Information related to inpatient referrals, adverse events, and mortality will be documented using study follow-up records.

The exploratory outcomes include the following:

Proportion of children with clinical infections based on clinical evaluation resultsProportion of children with subclinical infections assessed using hs-CRP, procalcitonin levels, blood culture, and urine cultureGrowth in stool culturePatterns of antimicrobial sensitivity and resistance among children with uncomplicated SAMHealth-seeking behavior, antibiotic usage patterns, and care preferences among caregivers of children with uncomplicated SAMChallenges and facilitators in the management of uncomplicated SAM, as perceived by health care providers

Blood, urine, and stool samples will be collected and processed using standard microbiological and laboratory procedures to assess infection status and AMR patterns. Qualitative data will be collected through FGDs and IDIs using semistructured interview guides.

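### The RCT's MUAC entry route disagrees with both of the protocol's SAM definitions, and because recovery is judged on WHZ alone, a MUAC-only entrant can meet the cure cut at enrolment

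*Protocol article*

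**What the plan says.** Four parts of the protocol article bear on this.

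- **Inclusion and Exclusion Criteria, Phase 3.** The anthropometric entry rule is WHZ below −3 SD "or MUAC=115 mm, (4) passing the appetite test using Balamrutham Plus". The same list requires "7) no edema, (8) no antibiotic use in the past 1 month".
- **Background.** Besides WHZ below −3 SD, SAM may be established by "a mid-upper arm circumference (MUAC) of <115 mm, or bilateral pitting pedal edema".
- **Operational Definitions.** "SAM is defined as WHZ<–3 SD of the median WHO child growth standards and/or by the presence of bilateral pitting edema". MUAC does not appear. Nonresponse is defined as "children who do not meet discharge criteria (WHZ>–2 SD) after 4 months".
- **Outcomes.** Nutritional status at follow-up, a secondary outcome, is "categorized as cured (WHZ>−2 SD), nonresponder (WHZ<−2 SD"), with loss to follow-up as the third category. Time to nutritional recovery is also secondary. MUAC at 16 weeks and 6 months is a primary outcome in its own right but forms no part of recovery.

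Phase 1 admits on WHZ at or below −3 SD with no MUAC route, and its participants may go on to Phase 3. The Phase 3 procedure expects another 150–200 children to be recruited after Phase 1 enrolment ends.

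**The concern.** The rule for entering the trial, the definition of the condition and the definition of recovery do not rest on the same measurement. Edema is barred at entry, so under the Operational Definitions only WHZ below −3 can make an RCT child a SAM case. A child admitted on MUAC with WHZ at or above −3 is outside that definition. At exactly 115 mm, the child is outside the Background definition as well.

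The statistical consequence lies in the recovery endpoints. No section requires a MUAC entrant to have WHZ at or below −2 at baseline or gives such a child a separate recovery rule. A child who starts above −2 and stays there is counted as cured whatever the treatment. That pulls the recovery proportions of the arms together and brings recovery times forward in every arm. Nutritional recovery is named in the third primary objective, so these outcomes matter although they are listed as secondary.

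**Working it through.** **1. The definitions applied to example children.** Each row is a hypothetical child without edema.

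| WHZ | MUAC (mm) | Enters RCT as written | Enters if sign is < | Enters if sign is ≤ | SAM, Background | SAM, Operational Definitions | Above −2 at baseline |
|---|---|---|---|---|---|---|---|
| −1.5 | 115 | yes | no | yes | no | no | **yes** |
| −2.5 | 115 | yes | no | yes | no | no | no |
| −1.5 | 112 | no | yes | yes | yes | no | **yes** |
| −2.5 | 112 | no | yes | yes | yes | no | no |
| −3.2 | 118 | yes | yes | yes | yes | yes | no |
| −3.0 | 118 | no | no | no | no | no | no |

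Under each reading of the sign, at least one child who enters is already above −2. Changing the sign only changes which child it is. The last row satisfies Phase 1 entry (≤ −3) but not Phase 3 entry (< −3), a small boundary mismatch.

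**2. How many children the route can reach.** The trial plans about 3 × 250 = 750 children, and Phase 1 enrols 606. 750 − 606 = 144, close to the 150–200 later recruits that the protocol expects. These are 150/750 = 20% to 200/750 = 27% of the trial.

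**3. How many would start above −2.** The documents give neither the share of the later stream entering on MUAC alone (s) nor the share of those with WHZ above −2 (h). Both are assumptions.

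- s = 20%, h = 50%: 150 × 0.2 × 0.5 = 15 to 200 × 0.2 × 0.5 = 20 children, or 15/750 = 2.0% to 20/750 = 2.7%.
- s = 100%, h = 50%: 75 to 100 children, or 10% to 13.3%.

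The later stream is allocated 1:1:1, so the first case means about 5 to 7 children per arm of 250.

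**4. Effect on the recovery difference.** If a fraction f of each arm starts and stays above −2, and the others recover with probability p, the observed proportion is f + (1 − f)p. The difference between two arms is then multiplied by (1 − f). With assumed recovery of 60% and 70% and 250 per arm:

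| f | Observed proportions | Difference (points) | Power |
|---|---|---|---|
| 0 | 60.0% vs 70.0% | 10.0 | 65% |
| 2% | 60.8% vs 70.6% | 9.8 | 64% |
| 10% | 64.0% vs 73.0% | 9.0 | 58% |

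At f = 2.7% the difference is 0.973 × 10 = 9.7 points, and at f = 13.3% it is 0.867 × 10 = 8.7 points. These are upper figures for dilution at each f, because they suppose that no such child falls back below −2.

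The sample size calculation is based on mean WHZ, not on recovery, so the plan has no recovery figure to reproduce.

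**The case against.** The strongest reply is that few such children would be randomized. Entry also requires enrolment in the SSFP/CMAM program. Children come from a tracking-system list of uncomplicated SAM, and home visits confirm the nutritional category. If that confirmation follows the Operational Definitions, a child with WHZ −1.5 and no edema would not be confirmed. This stands as a reason why the number is unknown and may be very small. It does not remove the inconsistency: the MUAC route would then be an entry criterion that admits nobody, and the protocol does not say which definition governs confirmation.

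Three stronger readings are tempting, and the documents do not support them.

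- **That children with low MUAC will be turned away.** This needs the equals sign to be meant literally. A continuous measurement required to equal one value is hardly workable, so a misprint is more likely.
- **That these children cannot fail, or recover at time zero.** Nutritional status is assessed at follow-up, and nonresponse after 4 months. A child who starts above −2 can deteriorate, be lost or die. Table 1 puts the first follow-up anthropometry at day 30, and no section counts the baseline measurement as recovery. Such a child would usually be counted as cured from that first visit.
- **That the primary comparison is biased.** Weight gain, WHZ and MUAC do not use the cure rule, and the later stream is randomized 1:1:1, so MUAC-only entrants are balanced across arms in expectation.

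**Conclusion.** The point holds as an inconsistency between eligibility, case definition and recovery definition, and it does not depend on how the equals sign is read. Its effect is dilution of cured/nonresponder status and time to recovery: about 2–2.7% under the modest assumption, and 10–13% if every later recruit entered on MUAC alone, in both cases with half of the MUAC-only entrants above −2. That half is itself assumed; the outer limit, with every later recruit above −2, is the stream's own 20–27%. A reader might suppose that 30% of recruits could enter on MUAC alone, but that is 225 children, more than the whole later stream.

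The bound relies on the forecast of 150–200. It would rise if fewer Phase 1 children than expected reach the RCT, which is possible because Phase 1 has started while the RCT is delayed, whereas Table 1 places RCT enrolment within 7 days of baseline.

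This should be corrected before RCT enrolment starts, as a consistency correction rather than a threat to the primary comparison.

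**What to change.** Reconcile the Background, the Phase 1 and Phase 3 inclusion criteria and the Operational Definitions so that trial entry and the SAM definition use the same index or indices with the same boundary, including the < −3 versus ≤ −3 difference. Which threshold is right is for the investigators to decide.

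If a MUAC route stays, add one analysis-set sentence: WHZ-based recovery, nonresponse and time to recovery are analysed in children who met the WHZ entry criterion at baseline, and MUAC-only entrants are reported on MUAC. The restriction uses a measurement taken before randomization, so the randomized comparison is preserved.

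The cost is an eligibility correction, one added sentence and a slightly smaller recovery analysis set. If the MUAC route is removed, the analysis-set sentence is not needed.
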